**Objectives**:

Primary trial outcomes are:

1. Comparison between trial groups of TB FREE SURVIVAL from two months after randomisation – to the final ascertainment visit among all household members identified at baseline – a total of 13 months. We will measure this in two ways; firstly, including all cases of where TB was diagnosed or multi drug TB treatment started, irrespective of the diagnostic method used and secondly, including only those with a hard copy of a laboratory confirmation of TB.

*Secondary trial outcomes*

1. Comparison between trial groups of the proportion of TB cases with diagnostic delay (defined as number of days between onset of symptoms and diagnosis of anti-tuberculosis treatment) among household members identified at baseline and diagnosed with TB between baseline and month 15
2. Comparison between trial groups of the prevalence of TB infection measured by tuberculin skin test reactivity >10mm at month 15 among household children identified at baseline and aged under 14 years of age.
3. Comparison between trial groups of the prevalence (reported as a percentage of those tested) of previously undiagnosed and untreated HIV infection among household members identified at baseline and again at month 15.
4. Comparison between trial groups of the cumulative incidence of all-cause mortality among all household members identified at baseline between baseline and month 15.
5. Comparison between trial groups of the cumulative incidence of TB- and HIV-related non-traumatic mortality among all household members identified at baseline between baseline and month 15.
6. Estimation of the cost-effectiveness of the intensified housed TB and HIV case-finding and prevention activities compared to the enhanced standard of care from a societal perspective. This will include comparisons of household costs and of quality of life of household members in the IHF and enhanced standard of care arms.

*Exploratory outcomes*

1. Cohort analysis of the incidence of bacteriologically-confirmed, and all-forms of tuberculosis among intervention group household members receiving and not receiving isoniazid preventive therapy, stratified by HIV serostatus.
2. Cohort analysis of the proportion of household members in the intervention group with previously undiagnosed HIV infection identified at baseline who successfully initiate antiretroviral therapy by month 15.

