## Procedures for all index case TB participants

After obtaining informed consent, enrolled nurses will administer a baseline index case demographic and clinical questionnaire (including presence and duration of symptoms, comorbid conditions, treatment received and laboratory confirmation of TB). Additionally, the study staff will obtain from each index case a handwritten household census comprising the first two letters of the first name and first two letters of the last name and ages and genders of all of their household members.

Index TB cases will continue to receive TB treatment and HIV testing and care through routine clinical services according to South African National Guidelines. Results of routine TB and HIV investigations completed by the health facility (sputum smear, sputum TB culture, Xpert MTB/Rif, HIV-test, CD4 count, HIV viral load), TB category (pulmonary, extra-pulmonary); and treatment initiation dates will be extracted from clinical records and recorded by study staff using data extraction forms).

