## Outcomes

*Primary trial outcomes*

1. Comparison between trial groups of TB FREE SURVIVAL from two months after randomisation – to the final ascertainment visit among all household members identified at baseline – a total of 13 months. We will measure this in two ways; firstly, including TB irrespective of the diagnostic method and secondly, including only bacteriologically-confirmed cases of TB.

*Secondary trial outcomes*

1. Comparison between trial groups of the incidence of all-forms of TB over months 2-15 among household members identified at baseline
2. Comparison between trial groups of the proportion of TB cases with diagnostic delay (defined as number of days between onset of symptoms and diagnosis of anti-tuberculosis treatment) among household members identified at baseline and diagnosed with TB between baseline and month 15
3. Comparison between trial groups of the prevalence of TB infection measured by tuberculin skin test reactivity >10mm at month 15 among household children identified at baseline and aged under 14 years of age. Analysis will be done overall and stratified by age.
4. Comparison between trial groups of the prevalence (reported as a percentage of those tested) of previously undiagnosed and untreated HIV infection among household members identified at baseline and again at month 15.
5. Comparison between trial groups of the cumulative incidence of all-cause mortality among all household members identified at baseline between baseline and month 15.
6. Comparison between trial groups of the cumulative incidence of TB- and HIV-related non-traumatic mortality among all household members identified at baseline between baseline and month 15.
7. Estimation of the cost-effectiveness of the intensified housed TB and HIV case-finding and prevention activities compared to the enhanced standard of care from a societal perspective.

*Exploratory outcomes*

1. Cohort analysis of the incidence of bacteriologically-confirmed, and all-forms of tuberculosis among intervention group household members receiving and not receiving isoniazid preventive therapy stratified by HIV serostatus.
2. Cohort analysis of the proportion of household members in the intervention group with previously undiagnosed HIV infection identified at baseline who successfully initiate antiretroviral therapy by month 15.

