Additionally, for secondary outcome 1, the analysis population will be restricted to those individuals aged less than 14 years at the time of outcome assessment at 15 months and for secondary outcome 2, the analysis population will be restricted to those individuals with a bacteriologically-confirmed TB diagnosis during the follow-up period.7. Subgroup analysis

Subgroup analysis by study site (Capricorn District and Botshabelo District) will be conducted for all outcomes, in order to assess whether the effect of the intervention differs between a high (Botshabelo) and lower (Capricorn) TB burden setting.

8. Recruitment and trial profile

A trial profile figure will be produced illustrating the following, by trial arm:

• Number of index cases screened for enrolment

• Number of index cases excluded, with reasons

• Number of index cases enrolled and randomised

• Number of household members identified at baseline

• Of those household members identified at baseline, number whose vital status can be ascertained at 15 months

• Of those household members identified at baseline, number for whom data on TB diagnosis is available at 15 months

9. Baseline characteristics and descriptive analyses

Characteristics of index cases, their households and household members identified at baseline will be tabulated and summarised by trial arm. Absolute number and proportions will be used for categorical variables, and means and standard errors, or medians and interquartile ranges will be used for continuous variables.

Characteristics to be summarised will include

Index case characteristics:

• Age

• Sex

• Source of index case

• Vital status

• Presence and duration of TB symptoms

• Treatment received

• Laboratory confirmation of TB

• Co-morbidities including HIV

• Employment status

• Income

Household characteristics:

• Number of household members

• Number of rooms, windows, external doors

• Household crowding

• Household construction materials

Household member characteristics

• Relationship with recruited index case

• Airspace sharing with recruited index case

• Presence and duration of TB symptoms

• History of previous and current HIV treatment

• History of previous and current TB treatment

• Employment status

• Income

10. Statistical analysis of outcomes

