Statistical analysis will be conducted using R (The R Foundation for Statistical Computing, Vienna, Austria) or Stata (StatCorp, College Station, Texas, USA). All analyses will employ statistical methods that allow for within-cluster (household) correlations. For all analyses, a 2-sided p-value<0.05 will be considered a statistically significant difference. No adjustment will be made for multiple testing.

Although baseline imbalance between the two intervention groups is unlikely due to the large sample size of this cluster randomised trial, the following situations will be considered as demonstrating imbalance in baseline covariates:

• More than 5% difference between the two arms in: % male and proportion of index cases with bacteriologically-confirmed pulmonary tuberculosis.

• More than 5 years difference in mean age.

• More than 1 person difference in mean number of household members

If there is no unbalance in covariates, study conclusions will be based on the unadjusted analysis described below. Otherwise, study conclusions will be based on analysis adjusted for imbalanced covariates as described below.

For the primary trial outcome (TB free survival), Poisson regression with random effects to account for clustering at the household level, will be used to estimate a rate ratio, 95% confidence interval and p-value for the effect of the intervention. To allow for the stratified randomisation by district, a fixed effect term for district will be included in the regression model. Where imbalance exists between trial groups (as defined above), these covariates will also be included in the regression model.

Analysis of secondary- and exploratory outcomes will follow a similar approach, except where binomial outcomes are assessed (e.g. proportion of child household members with MTB infection; proportion of household members with undiagnosed or untreated HIV), in which case we will use logistic regression with random effects to account for household clustering. For secondary outcome 5 (community HIV load), we will calculate this as the fraction of HIV-positive individuals with a measured viral load who have detectable viraemia multiplied by the number of individuals testing HIV-positive and divided by the total population with a measured HIV status.

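### The protocol analyses a secondary outcome, community HIV load, that it neither lists nor measures in contacts, and its number-based population rules do not match its own outcome lists

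*Protocol*

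**What the plan says.** Three rules in the Statistical analysis section identify secondary outcomes by number.

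- Under 10, Statistical analysis of outcomes: "For secondary outcome 5 (community HIV load), we will calculate this as the fraction of HIV-positive individuals with a measured viral load". The formula goes on to take the share of these with detectable viraemia, multiply by the number testing HIV-positive and divide by the number with a measured HIV status.
- Under 6, Analysis populations: "for secondary outcome 1, the analysis population will be restricted to those individuals aged less than 14 years".
- In the same sentence, secondary outcome 2 is limited to people with a bacteriologically confirmed TB diagnosis during follow-up.

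The protocol has two numbered lists of secondary outcomes. In the Outcomes section, item 1 is "Comparison between trial groups of the incidence of all-forms of TB over months 2-15 among household members identified at baseline" and item 5 reads "5. Comparison between trial groups of the cumulative incidence of all-cause mortality among all household members identified at baseline". In the Executive Summary, item 5 reads "5. Comparison between trial groups of the cumulative incidence of TB- and HIV-related non-traumatic mortality".

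Outside the formula, viral load is mentioned once, under Procedures for all index case TB participants. It is one of the routine results extracted from index cases' clinical records: "sputum smear, sputum TB culture, Xpert MTB/Rif, HIV-test, CD4 count, HIV viral load".

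**The concern.** An analysis rule tied to a number is only as good as the list it points to. Here there are two lists with different numbering, and the rules appear to follow a third. One rule concerns an outcome that is on no list and for which no contact data are described. Another restricts by age an outcome that both lists define without an age limit.

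What is at stake is the secondary comparisons. An undeclared outcome could appear in the report with no planned measurement behind it. The populations for all-forms TB incidence, diagnostic delay and skin-test infection would depend on which list the analyst takes as governing, and that choice should not remain open once data have been seen.

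**Working it through.** No figure in the plan is at issue, so the check sets the texts side by side.

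**Step 1: the two lists and the numbering that the rules imply.**

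| Number | Executive Summary | Outcomes section | Implied by the analysis rules |
|---|---|---|---|
| 1 | Diagnostic delay | All-forms TB incidence | Skin-test infection, by the under-14 limit |
| 2 | Skin-test infection | Diagnostic delay | Diagnostic delay, by the limit to TB cases |
| 3 | Undiagnosed and untreated HIV | Skin-test infection | not stated |
| 4 | All-cause mortality | Undiagnosed and untreated HIV | not stated |
| 5 | TB/HIV-related mortality | All-cause mortality | Community HIV load |
| 6 | Cost-effectiveness | TB/HIV-related mortality | not stated |
| 7 | none | Cost-effectiveness | not stated |

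The lists differ because the Outcomes section adds all-forms TB incidence as item 1 and shifts the rest down by one.

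**Step 2: match each rule.**

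- Rule for outcome 5: no match in either list.
- Rule for outcome 1: no match in either list.
- Rule for outcome 2: no match in the Executive Summary, a match in the Outcomes section.

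So 3 of 3 rules mismatch the Executive Summary and 2 of 3 mismatch the Outcomes section.

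**Step 3: can community HIV load be computed for contacts?** Let M be the HIV-positive people with a measured viral load, V those of them with detectable viraemia, P the number testing HIV-positive and N the number with a measured HIV status. The formula is (V/M) × P/N. The described sources for contacts are:

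- Intervention arm, baseline (HIV testing): rapid tests, PCR in infants, laboratory or oral-fluid alternatives, and a CD4 count if guidelines still require one. No viral load.
- Control arm: no contact between the one-week telephone call and the final visit. No viral load.
- Both arms, month 15 (final outcome assessment visit): repeat HIV testing for those negative or not previously tested. No viral load.
- Study Definitions: two HIV outcomes, based on testing and reported history or treatment. No viraemia outcome.

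For contacts, M = 0 under these procedures, so V/M is 0/0 and the measure is undefined in both arms.

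**Step 4: literal effect of the population rules.**

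- Outcome 1, Outcomes section: all-forms TB incidence loses every member aged 14 or over.
- Outcome 1, Executive Summary: diagnostic delay loses every TB case aged 14 or over.
- Outcome 2, Executive Summary: skin-test infection would be assessed only in people with confirmed TB.
- Outcome 2, Outcomes section: the rule reaches diagnostic delay, but both lists define delay among all members diagnosed with TB between baseline and month 15. Limiting it to bacteriologically confirmed cases drops those treated without confirmation, whom the Study Definitions count within all forms of TB.

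**The case against.** The best defence is that the content shows the intent. The bracketed label identifies community HIV load whatever its number, the under-14 limit plainly belongs to the skin test, and the limit to TB cases belongs to diagnostic delay. On this view the numbering is editorial, the primary outcome is untouched, and a separate analysis plan may settle the rest. Much of this stands, and it rules out several stronger readings.

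- A reader might infer that every number-based rule points to the wrong outcome. It does not: the outcome 2 rule lands on diagnostic delay in the Outcomes section.
- A reader might infer that the viraemia formula would be applied to deaths. The label makes that unrealistic.
- A reader might infer that community HIV load cannot be computed for anyone. Viral loads are extracted for index cases, and the formula speaks of individuals without naming contacts. The documents support only the statement that it is not computable for household contacts, the people to whom the trial-group comparisons in both lists refer.
- A reader might put a figure on the loss from the under-14 rule. If 30% to 40% of contacts were under 14, 60% to 70% would be dropped (100% − 40% and 100% − 30%). The protocol gives no age mix, so this is only an illustration.

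It could also be said that the final visit inspects patient-held records, which might hold a viral load. The items to be recorded from them are TB and HIV diagnoses, treatment and hospitalisations; viral load is not among them.

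The defence does not remove the core. The label confirms that an unlisted outcome was intended, and it leaves that outcome undeclared and unmeasured in contacts. The conflict over the delay population is one of substance and would survive renumbering. Nor is this detail left for later: the protocol states rules that contradict its own lists and procedures.

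**Conclusion.** The point holds in this form. Community HIV load has an analysis formula but is in neither outcome list, and the described procedures give no contact viral load in either arm. The under-14 rule for secondary outcome 1 matches neither list and, if followed, removes everyone aged 14 or over from all-forms TB incidence or diagnostic delay. The confirmed-TB rule for secondary outcome 2 fits one list and not the other, and where it fits it still narrows the stated population.

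The effect is confined to secondary outcomes. Its size in participants cannot be derived, because the protocol gives neither the age distribution of contacts nor the share of TB cases without confirmation. The conclusion rests on two assumptions: that the procedures described are complete as to viral load, and that secondary outcomes concern household members, as both lists say apart from the cost-effectiveness item. It is worth correcting before analysis, mainly for the unlisted outcome and the delay population; the numbering by itself would be editorial.

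**What to change.** 1. Keep one numbered list of secondary outcomes, the same in the Executive Summary and the Outcomes section, and refer to outcomes by name in the analysis text.
2. Apply the under-14 restriction only to skin-test infection, and state that all-forms TB incidence is analysed in all household members.
3. Decide whether diagnostic delay covers all diagnosed TB or only bacteriologically confirmed TB, and say the same in the outcome lists and under Analysis populations.
4. Delete the community HIV load sentence, since no contact viral load is described. The exception is if the sponsor already collects contact viral loads in both arms; in that case list the outcome and describe its measurement.

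The cost is protocol wording. Deletion gives up nothing that the described procedures could measure in contacts. Keeping the outcome means declaring it and documenting its data source.

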# Study Administration and Monitoring

**IRB Approval**Ethical approval will be sought from Institutional Review Board of the University of the Witwatersrand, South Africa, the University of Liverpool, UK, and the London School of Hygiene and Tropical Medicine, UK.

**Trial Registration**
The trial protocol (and all subsequent amendments) will be registered on the clinicaltrials.gov website in the South African equivalent prior to commencement of study activities.

**Trial Steering Committee**
We will establish a Trial Steering Committee, comprising of the Trial Principal Investigators, Trial Statistician and Project Manager who will assume responsibility for the trial management and conduct.

**Data and Safety Monitoring Board**
We will establish a Data and Safety and Monitoring Board (DSMB) comprising of external experts, including a statistician experience in cluster-randomised controlled trials in sub-Saharan Africa, a clinical scientist experienced in TB management, and a lay member. The DSMB will meet four times: once prior to commencement of study activities; twice during the 15 month trial activity period, and once following completion of analysis. At each meeting, the DSMB will review a Trial progress report describing rates of recruitment and uptake of trial interventions, outcomes, and serious adverse events recorded. Because of the short duration of study activities, and the low potential for harm, interim analysis will not be performed.

**Good Clinical Practice**
All study staff members will complete study specific clinical trial research training provided by Perinatal HIV Research Unit, and will be required to have certification to demonstrate proficiency to Good Clinical Practice (GCP) Standards.

# Available Infrastructure

***PHRU: Matlosana:*** The North West Department of Health has provided office and clinic space to PHRU, at the Tshepong Hospital in Klerksdorp. Classified as a regional hospital, its immediate catchment area is Matlosana but also takes referrals from further afield. There are four towns and their adjacent townships in Matlosana, with a total population of about 750,000. The Matlosana health sub-district treats about 5000 TB patients each year, diagnosed in its 16 clinics and the hospital. HIV coinfection in adults is 85%, almost 90% of women diagnosed with TB being co-infected with HIV. Adult medicine admits about 40 patients per day, approximately half with infected with HIV and approximately one third of all admissions will either be receiving treatment or diagnosed with TB. PHRU established a research presence seven years ago, and now employs over 130 staff conducting research into several important TB-related areas. We currently recruit MDR patients to clinical trials of novel TB agents at the the purpose-built, drug resistant in-patient TB wards, capable of treating 100 in-patient MDR, and 20 XDR TB cases.

The hospital has a well-equipped accredited NHLS laboratory, capable of doing Xpert MTB/Rif and liquid culture. PHRU has daily courier service to research laboratories in Johannesburg. The Matlosana sub-district diagnoses PHRU has a research presence in all clinics of the Matlosana health sub-district, and in the hospital, there is an active surveillance program identifying all cases of TB either diagnosed through positive laboratory tests or started on empiric TB treatment. It will be relatively easy to include in this study only TB cases identified in the Jouberton township immediately adjacent to the Tshepong Hospital.

In the **Polokwane Municipality in Capricorn Health District, Limpopo Province,** we will establish a study office in the Department of Medicine, University of Limpopo, under the leadership of [name]. The populations size is larger and demographics are similar to those of Matlosana, but the epidemiology of HIV and TB is very different. As PHRU has done in Klerksdorp, we will support and develop the creation of a research facility in Polokwane. Not only will we ensure that both the study staff and those in the Department of medicine receive research and GCP training, but also will assist [name] in applying for other grants, research projects and turning research findings into publications. We have already conducted a pilot study of household contact tracing, recruiting 130 index cases in 23 clinics around Thouyandou, in Limpopo, are implementing a cluster randomized trial in the area of Vhembe around Makhado, and are conducting further research in household contact tracing with [name] in the Vhembe and Waterberg Health Districts in Limpopo. This study will include the local teaching hospital as an active partner.

